### Analyses

An intention-to-treat analysis along with a secondary per-protocol analysis will be carried out. Descriptive statistics will assess the adequacy of patient characteristics and balancing of the randomization process. Inferential analysis will employ Student’s *t* test and Chi-square testing. Survival analysis using the Kaplan–Meier method will be used to assess stent patency time. A step-wise multivariate regression analysis will be undertaken to identify independent predictors of stent dysfunction and adverse events using a log-rank test. A *p* value of 0.05 or less will be considered statistically significant. All analyses will be performed using SAS version 9.4. No interim analysis is planned given the short accrual time, relative small sample size, and short follow-up period.

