## Methods

### Design and objectives

The Eus-guided biliary drainage with LumEn apposing Metal stENT vs. ercp (ELEMENT) trial is a multicenter prospective randomized controlled trial, across nine sites in Canada, comparing EUS-CDS with a biliary LAMS vs. ERCP in the initial endoscopic management of malignant distal biliary obstruction (Fig. 1). We hypothesize that EUS-CDS using LAMS is associated with fewer episodes of stent dysfunction and need for re-intervention when compared to standard ERCP while being comparable in safety and technical success in patients with malignant distal biliary obstruction (Additional file 1). At the time of writing this manuscript, this trial has been approved by the IRB of the coordinating center and two additional participating sites. All other sites have submitted their IRB application and will only start patient recruitment once approved.

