### Randomization

Patients included are randomized in a 1:1 ratio, in blocks of four, stratified by site and resectability: borderline resectable/locally advanced versus unresectable malignant distal biliary obstruction (Fig. 2 via secure Internet software (randomize.net)). Patients are randomized by a research assistant following consent. The endoscopist is then informed of the treatment allocation and the research nurse will verify that the correct assigned procedure is carried through and documented.

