### Endpoints

The primary endpoint is the rate of stent dysfunction (including both migration and occlusion) needing endoscopic or radiological re-intervention (Table 2). Patients who reach the primary endpoint are considered to have completed the study once hospitalization time for stent dysfunction and delays in chemotherapy treatment have been captured. Patients who do not reach the primary outcome are followed until surgery, death, or up to 1-year post stent insertion.

**Table 2 Tab2:** Criteria for primary endpoint of stent dysfunction

Meeting one or more of the following criteria:	
□ Suspected cholangitis [13]	
□ Definite cholangitis [13]	
□ 50% increase in bilirubin from the lowest level post index procedure	
□ 20% increase in bilirubin from the lowest level post index procedure AND evidence of obstruction on imaging (US/CT/MRI)	
AND:	
□ Endoscopic or radiological re-intervention confirming stent blockage or migration needing stent cleaning, stent change, and/or additional stent insertion

**Table 3 Tab3:** Secondary endpoints

1. Technical success defined as successful insertion of a transpapillary stent or choledochoduodenostomy stent at the initial procedure at time of randomization [6–8]	
2. Clinical success defined as 50% decrease in bilirubin < 2 weeks post-stent insertion or less than 25% of pre-procedure bilirubin level within 4 weeks post stent insertion [6]	
3. Stent patency defined as mean time to stent obstruction or migration (patient will be censored at last-follow-up or death)	
4. Proportion of patients with interruptions in chemotherapy treatment due to recurrent stent dysfunction	
5. Early adverse events (within 14 days of index procedure) as defined per the ASGE lexicon for endoscopic adverse events [18], including post-procedural pancreatitis, bleeding, intestinal perforation, and cholangitis	
6. Delayed adverse events (greater than 14 days of index procedure until last follow-up or death)	
7. Cost-effectiveness analysis	
Additional outcomes	
1. Median number of days in delayed chemotherapy treatment if interrupted	
2. Procedure time defined as from insertion of the endoscope to endoscope withdrawal1	
3. Fluoroscopy time	
4. Rate of hospitalization and length of stay	
5. Mortality	

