##### Primary endpoint

Rate of re-intervention: Based on RCT data and retrospective series using LAMS [6–8, 10–12], we estimate a re-intervention rate of 30% vs. 10% for the ERCP and EUS-BD groups, respectively up to a 1-year follow-up period. To achieve a statistical power of 80% with a two-sided type I error of 5%, a total of 124 patients (62 in each arm) is required. Taking into account a 5% dropout rate, a final sample of 130 patients (65 patients in each arm) is needed.

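### Randomisation is stratified by site and resectability but the named between-arm tests use neither factor; if these factors predict stent dysfunction, the chi-square is conservative and forgoes a little power

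*Protocol article*

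**What the plan says.** Under Randomization in the protocol article, patients are "randomized in a 1:1 ratio, in blocks of four, stratified by site and resectability". Resectability has two levels. Design and objectives places the trial "across nine sites in Canada", so there are up to 9 × 2 = 18 strata.

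Under Endpoints, "The primary endpoint is the rate of stent dysfunction (including both migration and occlusion) needing endoscopic or radiological re-intervention". This is a proportion per arm, and the sample size section treats it as one: "we estimate a re-intervention rate of 30% vs. 10% for the ERCP and EUS-BD groups".

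Under Analyses, inference is to use Student's t "test and Chi-square testing". Kaplan–Meier is named for stent patency. One model is named: "A step-wise multivariate regression analysis will be undertaken to identify independent predictors of stent dysfunction and adverse events". The section does not mention the stratification factors, and it does not tie a test by name to the primary endpoint.

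**The concern.** Stratified allocation makes the arms more alike on site and resectability than simple randomisation would. If those factors predict the outcome, the true variance of the difference between arms is smaller than the one the ordinary chi-square uses. The test then rejects too rarely under the null, its interval is too wide, and some power is forgone.

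The document gives some reason to expect prognostic strata. Follow-up ends at surgery or death, and both should depend on resectability. Stent type, stent size and sphincterotomy in the ERCP arm, and stent size in the EUS arm, are left to the endoscopist, so practice may differ between sites.

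The step-wise regression does not close the gap. It is a search for predictors rather than the treatment comparison, and step-wise selection need not keep the design factors.

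**Working it through.** **1. The plan's own figure.** Inputs from the Primary endpoint part of the sample size section: 30% v 10%, 80% power, two-sided 5%. With pooled variance, mean rate 0.20 and no continuity correction:

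n per arm = [1.96·√(2·0.20·0.80) + 0.8416·√(0.30·0.70 + 0.10·0.90)]² / 0.20² = (1.1087 + 0.4610)² / 0.04 = 61.6, so 62.

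This matches the stated 62 per arm (power 80.3%; 82.1% at 65 per arm). The unpooled formula gives 59 and the continuity-corrected one 72. The trial was therefore sized for an unstratified, uncorrected chi-square.

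**2. Direction, by hand.** Take resectability alone, two equal strata, exact balance, and the same risk in both arms.

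- Null risks 30% and 10% (odds ratio 3.9): the chi-square uses 0.20·0.80 = 0.160; the true within-stratum variance is (0.21 + 0.09)/2 = 0.150. The ratio is 0.9375, so the statistic has SD √0.9375 = 0.968. Size = 2·P(Z > 1.96/0.968) = 2·P(Z > 2.024) = 4.3%.
- Null risks 38% and 4% (odds ratio 14.7): 0.21·0.79 = 0.1659 against (0.2356 + 0.0384)/2 = 0.137. The ratio is 0.826 and the SD 0.909. Size = 2·P(Z > 2.157) = 3.1%.

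Simulation of these two cases gave 4.2% and 2.9% for the chi-square, against 5.0% for the Mantel-Haenszel test.

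**3. Size over a range.** The strength of the strata is an assumption throughout. Simulation: N = 124, nine sites of equal expected size, two equally common resectability levels, blocks of four within stratum, a common treatment effect on the log-odds scale, 20,000 trials per row. Marginal rates are 30%/10% for power and 20%/20% for size. CMH is the Cochran-Mantel-Haenszel test over all 18 strata or over resectability only.

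| Site SD (log-odds) / resectability OR | Power: chi-square | Power: CMH, 18 strata | Power: CMH, resectability | Size: chi-square | Size: CMH, 18 strata |
|---|---|---|---|---|---|
| 0 / 1 | 81.7% | 80.6% | 81.4% | 5.2% | 5.0% |
| 0.3 / 1.5 | 82.0% | 81.5% | 81.9% | 4.8% | 4.8% |
| 0.5 / 2 | 81.6% | 81.9% | 81.7% | 4.7% | 4.9% |
| 0.8 / 3 | 82.1% | 83.7% | 82.8% | 3.9% | 5.1% |
| 1.2 / 5 | 84.2% | 88.5% | 85.4% | 3.3% | 5.2% |
| 1.5 / 9 | 84.8% | 90.9% | 86.7% | 2.2% | 4.9% |

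The Monte Carlo standard error is about 0.3 points for power and 0.15 points for size.

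A second simulation, with about 65 per arm, site SD 0.8 and a resectability effect of 1.2 on the logit scale (odds ratio e^1.2 = 3.3), gave size 3.7% v 5.0% and power 80.7% v 83.1%. That is in line with the 0.8 / 3 row.

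**4. Sparse strata.** 124/18 = 6.9 patients per stratum. At a 20% overall event rate that is about 1.4 events each. A stratum with no events contributes nothing to the CMH test, which is why the full 18-stratum version loses about a point when the factors carry no information.

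**The case against.** The Analyses wording is one generic line for all endpoints. It neither assigns the chi-square to the primary endpoint nor calls it unstratified. Agreement with 62 per arm proves little, because trials are often sized without strata and analysed with them. A fuller analysis plan, not shown, may adjust. All of this is fair, and it limits how firmly the point can be put. What remains is that the article does name its tests, that only the chi-square fits a binary rate, and that nothing in the section brings in the design factors. If a fuller plan adjusts, the article should say so.

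The prognostic argument is also uncertain. Surgery should shorten time at risk mainly in borderline or locally advanced disease, and death mainly in unresectable disease. On a binary endpoint the two could partly cancel. The document gives no figure for either factor.

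A reader might infer that the true type I error is below 5% and that power is being lost as a matter of fact. The document does not support that: in the first three rows of the table, size is 4.7–5.2% and the 18-stratum test ranges from about 1 point worse to 0.3 points better. Nor does it follow that the trial is underpowered, because the chi-square stays above 80% in every scenario. Nor is the protection of stratified allocation wasted: balanced arms already benefit the unadjusted estimate, and only its estimated variance fails to show it.

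**Conclusion.** The mismatch between a stratified design and unstratified named tests stands, and so does its direction: any error is conservative, and only if the strata are prognostic. Its size depends on a strength the document does not give. From no effect up to site SD 0.8 and an odds ratio of about 3, chi-square size runs from about 5% to about 3.5–3.9%, and a stratified test changes power by about −1 to +2 points. Gains of 4.3 and 6.1 points need both factors to be very strong (1.2 / 5 and 1.5 / 9). Type I error is not inflated and the stated sample size is right for the test it implies. This is a modest improvement in efficiency and consistency, worth making because it costs so little.

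**What to change.** State in Analyses that the primary endpoint is compared with a Cochran-Mantel-Haenszel test and a Mantel-Haenszel risk difference (95% CI), stratified at least by resectability. Add site only after low-enrolling sites have been pooled by a rule, with its threshold, written down before unblinding. Keep the unstratified chi-square as a supportive analysis, and stratify the comparison of stent patency in the same way.

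The cost is one sentence and one procedure option, since both factors are recorded at randomisation. If the factors turn out not to be prognostic, resectability alone gives up about 0.3 points of power (81.7% v 81.4%) and all 18 strata about 1 point (81.7% v 80.6%). Resectability alone gains up to 1.9 points in the strongest scenario (86.7% v 84.8%). The choice has to be fixed in advance, because choosing between adjusted and unadjusted results after seeing the data would be open to challenge.

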### Data collection

Collected data include primary, secondary (Table 3), and additional endpoints listed above, demographics, ASA score, Karnofsky index, type of sedation used, laboratory investigation including complete blood count, coagulation profile, liver enzymes, tumor staging based on the TNM classification for pancreatic cancer, quality of life data using the EQ-5D, peri-endoscopic data such as use of rectal indomethacin, antibiotics, and technical details including type of endoscope, EUS and ERCP accessories including stent type and size, sphincterotomy or tract dilation performed prior to stent insertion. Data are collected at the index procedure, and also at days 7, 30, 90, 180, 270, and 1 year post-randomization.

All data will be collected by research personnel who have been previously trained to use both the randomization website (randomize.net) and the data capturing software (redCAP). These research personnel are also GCP (Good Clinical Practices) and SOP (Standard Operating Procedures) certified. All data collected will be de-identified, meaning that information such as name, date of birth, hospital identifier, and Medicare number will not be stored in the main database. Each participant will be referred to by their study number. There will be a separate file stored in a password protected and encrypted computer with the decoder of identifiables in case these patients need to be contacted. All data will be stored for 7 years after publication or as requested in Standard Operating Procedure (SOP) from individual sites. Only data relevant to the study as outlined in this protocol will be collected by the research team. All information collected during the research project will remain confidential.

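### The log-rank test is attached to a stepwise regression that it cannot serve, and about 26 expected dysfunction events are too few for stepwise selection of predictors

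*Protocol article*

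**What the plan says.** The Analyses section of the protocol article plans an intention-to-treat analysis with a secondary per-protocol one, t and chi-square tests for inference, and Kaplan–Meier for stent patency. It then adds: "A step-wise multivariate regression analysis will be undertaken to identify independent predictors of stent dysfunction and adverse events using a log-rank test". That sentence is the only place where a log-rank test appears. It names no regression model for either outcome and gives no list of candidate predictors. The only significance level in the section is 0.05.

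Three other places bear on the point:

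- **Table 3** separates early adverse events, counted within 14 days of the index procedure, from delayed ones, which run to last follow-up or death.
- **Data collection** records patient status scores, laboratory panels, tumour stage, sedation and prophylactic drugs, and also "technical details including type of endoscope, EUS and ERCP accessories including stent type and size, sphincterotomy or tract dilation performed".
- **Sample size calculation, Primary endpoint** gives the planning rates: "we estimate a re-intervention rate of 30% vs. 10% for the ERCP and EUS-BD groups, respectively up to a 1-year follow-up period". It needs 62 patients per arm for 80% power at a two-sided 5% level, and then "Taking into account a 5% dropout rate, a final sample of 130 patients (65 patients in each arm) is needed".

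The Randomization section says: "Patients included are randomized in a 1:1 ratio, in blocks of four, stratified by site and resectability".

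**The concern.** The sentence joins two things that do not fit. A multivariable regression estimates the effect of each covariate adjusted for the others, and that adjustment is what the word independent claims. A log-rank test compares survival curves between groups and estimates no adjusted effect. For early adverse events the mismatch goes further, because a yes/no outcome over a fixed 14-day window calls for a binary model, not a test on survival curves. A reader cannot tell which model will be fitted to which outcome.

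The second difficulty is the stepwise selection, which is stated outright. With few events and many possible candidates, such a procedure tends to pick up noise, and the p-values of the retained variables are too small because they ignore the search. At stake is whether the predictors of stent dysfunction and adverse events that the trial reports can be believed.

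The third concerns the technical variables. Their values are either set by the arm or not comparable across arms, so in a pooled model they would be entangled with treatment.

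**Working it through.** **1. The plan's own sample size.** Inputs: 30% and 10%, two-sided 5%, 80% power. The pooled-variance formula for two proportions has mean rate 0.20:

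n per arm = [1.96 × √(2 × 0.20 × 0.80) + 0.8416 × √(0.30 × 0.70 + 0.10 × 0.90)]² / (0.30 − 0.10)² = (1.109 + 0.461)² / 0.04 ≈ 61.6, so 62.

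This matches the stated 62 per arm and 124 in total. The power at 62 per arm is 80.3%. The rates and the sample size are therefore consistent with each other and can be used for an event count.

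**2. Expected stent dysfunction events.** The article does not state this count. It follows from the same inputs:

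- all 130 patients: 65 × 0.30 + 65 × 0.10 = 19.5 + 6.5 = 26.0
- 124 evaluable patients: 62 × 0.30 + 62 × 0.10 = 18.6 + 6.2 = 24.8

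In simulated trials with 65 per arm and these rates, the count fell between about 17 and 36 in 95% of trials.

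**3. Chance of a false predictor.** Assumptions: k independent candidates with no real effect, each screened at 0.05. The entry level is not stated; 0.05 is the only threshold in the section. The number of candidates is not stated either, so k = 5, 10 and 15 are shown. The closed form is 1 − 0.95^k. The simulation used 600 trials per setting, 65 per arm, rates of 30% and 10%, arm forced in, and stepwise logistic regression with entry and stay at 0.05.

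| k | Events per candidate (26/k) | 1 − 0.95^k | Simulated chance of at least one false predictor | Mean false predictors per trial |
|---|---|---|---|---|
| 5 | 5.2 | 23% | 26% | 0.29 |
| 10 | 2.6 | 40% | 43% | 0.57 |
| 15 | 1.7 | 54% | 54% | 0.82 |

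**4. Adverse events.** The article gives no planning rate. Its only figure is 7%, from a retrospective LAMS series cited in the Discussion. If 7% held in both arms (an assumption), 130 × 0.07 = 9.1, about 9 events. At an assumed 15%, 130 × 0.15 = 19.5, about 20.

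**5. What the event count can support.** Ten events per parameter is a conventional figure and is assumed here. It gives 26 / 10 = 2.6, so two parameters.

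- arm and resectability: 26 / 2 = 13 events per parameter
- one further covariate: 26 / 3 = 8.7
- arm, resectability and nine sites as fixed effects (1 + 1 + 8 = 10 parameters): 26 / 10 = 2.6

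For a stratified log-rank test, the randomisation factors give up to 9 × 2 = 18 strata, or 26 / 18 ≈ 1.4 events each. Stratifying by resectability alone leaves two strata.

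**6. Technical variables by arm.** The EUS-BD section allows LAMS sizes of 8 × 8 or 6 × 8 mm. The ERCP section allows 10 × 40, 10 × 60 or 10 × 80 mm, with the choice of covering and of sphincterotomy described there only. Stent size is recorded in both arms but no value is shared, so in a pooled model it identifies the arm.

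**The case against.** The strongest reply is that the sentence is loosely worded but not meaningless. The log-rank statistic is the score test of a Cox model with one factor, and score statistics are commonly used to admit variables in stepwise Cox selection. Log-rank screening followed by a Cox model may have been meant, or the clause may have slipped from the preceding Kaplan–Meier sentence. This stands to the extent that a reader should not conclude that no version of the analysis could ever be fitted. The text names no Cox model and no screening step, however, and neither reading suits early adverse events in a fixed window. A later analysis plan could not merely add detail to this sentence; it would have to correct it.

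Four stronger readings are tempting and are not supported:

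- **Patency has no between-arm test.** The article names none beside Kaplan–Meier, but a condensed article may leave that to the analysis plan.
- **The treatment effect will come from a model chosen by the data, or arm will be dropped.** The stated purpose is to find predictors. The primary comparison has its own intention-to-treat analysis, and chi-square testing is available for it. Nothing says that the arm effect will be read from the stepwise model.
- **The technical variables exist in one arm only.** That is wrong for stent size. They also appear in a data-collection list; no section names them as regression candidates.
- **The false-predictor risk is 40%.** That holds only for exactly 10 independent null candidates. Variables collected are not the same as variables screened.

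It is also fair to say that predictor identification is not among the primary, secondary or additional endpoints.

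**Conclusion.** The point holds in a limited form. The log-rank wording is a stated method that is wrong as written, and this does not depend on any assumption. Stepwise selection is a poor choice with 26 expected dysfunction events (24.8 with 124 evaluable patients), a count that rests on the plan's own rates. The chance of at least one false predictor, about 23% to 54%, is illustrative: it assumes 5 to 15 independent null candidates and an entry level of 0.05. The figure of about 9 adverse events assumes that 7% applies in both arms.

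The analysis is secondary. A reader might infer that the trial's main conclusion is at risk; it is not, since the primary comparison and the sample size do not depend on this sentence. The correction is worth making because it is cheap and should be settled before the data are analysed.

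**What to change.** Replace the sentence in the Analyses section with four statements:

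1. Stent patency is compared between arms with a log-rank test stratified by resectability, alongside the Kaplan–Meier curves. Site is left out of the strata because the events are too sparse.
2. Stepwise selection is dropped in favour of prespecified models. For time to stent dysfunction, fit a Cox model with arm forced in and resectability as the only covariate. For adverse events, fit a logistic model with arm only, or use penalised estimation if a covariate is added. The logistic model fits the early events with their fixed window; if delayed events are modelled too, their unequal follow-up should be allowed for.
3. Stent type, stent size and sphincterotomy stay out of the pooled model and are examined only within arm.
4. The predictor analysis is labelled exploratory.

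The cost is a change of wording and less data-driven output. No extra patients or data are needed.

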#### Cost-effectiveness analysis

A decision tree will be created for the two possible biliary drainage approaches over a 6-month time horizon. Probability assumptions will be extracted from the RCT and the unit of effectiveness will be cost per QALY. Costs will be determined from chart data abstraction of patients in each group to determine resource consumption. The regie de l’assurance maladie du Quebec (RAMQ) and institutional database relating to professional fees, hospitalization (where appropriate), and equipment accounting for direct costs will be utilized. Third-party costs related to the procedure and downstream management costs will be determined based on the RCT resource utilization data. Deterministic and probabilistic sensitivity analyses will be undertaken to assess the robustness of the findings.

